### Recruitment {15}

Participants will be recruited from nephrology outpatient departments across the study sites, with the principal investigator, or delegate, identifying potentially eligible individuals from their respective hospital databases. A study invitation letter and information summarising the study may be used by site research staff to inform potential participants that, during an upcoming clinic appointment, they will be approached by their nephrologist, research nurse or delegate about participating in the trial. The letter will include contact information for the research nurse or delegate, should the individual wish to make enquiries about participating.

During clinic appointments, the site’s principal investigator, or delegate will approach prospective trial participants to introduce the trial, describe the study, and answer any questions. This may occur face-to-face or over the phone, depending on the delivery mode of the clinic.

Strategies to achieve adequate participant enrolment include providing clear information in a user-friendly format that outlines the aims of the trial, the individual’s required commitment, and how it is anticipated the research will help people such as them in the future. This will be underpinned by the Consumer Advisory Board reviewing trial participant materials. Other strategies include clear information on who the local contact is for the trial at each site and the provision of a timely response to any questions from prospective participants. Culturally and linguistically diverse patients are accommodated by an interpreter service being available for recruitment and all study assessments.

## Assignment of interventions: allocation

### Sequence generation {16a}

The participating clusters will be randomised to the intervention or control group with an allocation ratio of 1:1, using a block randomisation schedule generated by an independent unblinded statistician.

### Concealment mechanism {16b}

The allocation list will be maintained on a secure server in a folder accessible only to the independent statistician and the block size will be concealed from all other personnel involved in the study.

### Implementation {16c}

All participants at a cluster randomised to an intervention group will receive the intervention, CGA. Participants at a cluster randomised to a control group will receive usual care.

## Assignment of interventions: blinding

### Who will be blinded {17a}

Due to the nature of the intervention complete blinding is not feasible. Therefore, clinicians and participants will not be blinded to the treatment allocation. However, researchers assessing the outcome, responsible for the analysis and reporting of the study (including the lead statistician, lead data manager and trial steering committee members) will be blinded to the allocation of the two intervention arms.

### Procedure for unblinding if needed {17b}

The Data and Safety Monitoring Board and the independent statistician will make recommendations to the Trial Steering Committee, as required, should safety monitoring warrant unblinding.

## Data collection and management

### Plan for assessment and collection of outcomes {18a}

The research nurses or delegate at each study site will be primarily responsible for data collection and data entry, as per the timings overviewed in Fig. 1. They will collect baseline and clinical assessments by meeting with each study participant and reviewing their medical record. They will also administer the GAS, EQ-5D-5L, and FI tools. Data will be directly inputted into Research Electronic Data Capture (REDCap), a secure, web-based software platform hosted at The University of Queensland [39]. Training on data collection processes and the use of REDCap will be provided by the coordinating centre at site initiation.

Given GAS is the primary outcome measure and concerns exist regarding implementation due to the risk of poorly written goals and scales [40–42], a comprehensive training package was developed. This training was designed to ensure the consistent application of GAS by enabling research nurses and delegates to administer it confidently and competently. Supplementary file 4 provides an overview of the training that was provided, which included simulated cases and direct one-on-one feedback.

#### Goal attainment scaling

GAS will be used to measure attainment of patient-identified goals as it is suitable in potentially heterogenous patient groups with differing goals [43, 44], and has been found to be a valid [43, 45, 46], reliable [45, 46], and responsive [25, 47, 48] outcome measure. It has been advocated as a sensitive measure of change in trials of complex interventions for frail older people [25, 49, 50]. As a method of setting measurable goals which are meaningful for patients, it is highly congruent with principles of personalised medicine [51].

The basic steps of GAS include: identifying goals; defining the current (baseline) status; identifying potentially better and worse attainment outcomes on a five-point scale, with consideration of patient and environmental factors such as their current status; weighting the goals; and, at follow-up, scoring the achieved outcome against the stated possible attainment levels [52].

The extent to which goals are achieved is calculated by the formula [53]:$$\mathrm{GAS score}=50+ \frac{\left[10 \sum \left({w}_{i}\times {x}_{i}\right)\right]}{\sqrt{\left[0.7 \sum {w}_{i}^{2}+0.3 {\left(\sum { w}_{i}\right)}^{2}\right]}}$$where $${w}_{i}$$ = weight assigned to the goal area and $${x}_{i}$$ = the attained score for the goal area.

Using this formula, a score of 50 means that all goals have been met. Scores lower than 50 show a deficit in goal attainment, and scores above 50 show better-than-expected outcomes [53]. The overall score is normalised to a mean of 50 and a standard deviation of 10.

#### EQ-5D-5L

Quality of life will be measured by EQ-5D-5L (EuroQol 5 dimensions, 5 levels questionnaire) as it is a frequently used and validated quality of life instrument [54]. The measure also allows comparisons with international data and conversion to a utility score for use in the economic analysis of the intervention.

#### Frailty index

There is a lack of consensus as to how to measure frailty, with a systematic review identifying 20 different frailty instruments used for people with CKD [12]. The FI has been selected for this study as it has been confirmed to be feasible and valid for older people with CKD in the outpatient setting [29]. It also has the degree of granularity necessary to inform decision-making for individuals, which is lacking where dichotomous classifications of frail/not frail are used [29]. Further, it recognises frailty as a multidimensional risk state and, in doing so, it can facilitate quantification of its severity across the health spectrum [29, 55–58].

#### Health care use analysis

Health care use, and their associated costs, will be calculated from the Health Care Diary (see Supplementary file 5) completed by participants and from hospital records when available. The unit cost of care will be derived from appropriate sources for different types of services. For primary care, including specialist visits, the Medicare schedule with estimated out-of-pocket expenses will be applied. For hospital stay, (average) unit cost associated with respective Australian Refined Diagnosis Related Groups (AR-DRG) will be applied. Other costs will be applied at appropriate market wages for the care provided.

#### Patient recall of health service utilisation

Count of service used by health service types collected from the Health Care Diary (participant-completed) will be compared to services recorded and retrieved from data linkage.

#### Process evaluation

At the end of the 12-month follow-up period, qualitative semi-structured interviews will be conducted with ~ 30 purposively sampled patients and their caregivers until data saturation is achieved. Key informant interviews will also be conducted with clinicians (geriatricians, nephrologists, general practitioners, nurses, allied health professionals) involved in the study, with the final number determined by that needed for thematic saturation. All interviews will be recorded and transcribed verbatim.

Additionally, data will be extracted from redacted CGA letters/reports obtained from intervention sites to allow for analysis of the main health and wellbeing issues identified in the CGA and any associated recommendations made by the Geriatrician to address them. An issues register will also be kept by the coordinating centre to capture any observations that can inform the process evaluation.

#### Safety

Data collected for the secondary outcomes related to mortality and associated hospital admissions will be used for monitoring participant safety.

### Plans to promote participant retention and complete follow-up {18b}

Participant retention will be achieved by several strategies. Participant involvement throughout the trial development, activation and conduct, facilitated primarily by obtaining the Consumer Advisory Board’s input, ensures a patient-centred approach is applied to all trial activities and interactions with trial participants. The study staff at each site will be accessible to participants to answer their questions and respond to any concerns. To minimise the burden on a participant’s time, study visits will be scheduled to occur with any pre-existing clinic or other outpatient appointments in place for them when possible. Parking vouchers or travel reimbursements, to a maximum of $60 AUD, will be provided for visits that are study-specific and cannot be done remotely over the phone. Practical guidance and suggestions for participant retention awareness training will occur at the site initiation meetings and is documented in the Operations Manual.

For participants who withdraw from the trial, no further information will be collected from the date of withdrawal. If a participant at an intervention site does not receive the CGA, or a participant at the control site receives a CGA, they will remain in the trial and be followed up until the end of the study and analyses will be conducted using the intention-to-treat principle.

### Data management {19}

Study data will be captured and stored in a REDCap database, which is secure, and password protected. The trial’s data management team will utilise REDCap’s Data Quality module, complemented by R statistical software (R version 4.1.0) [59], for data cleaning and to ensure data completeness, plausibility, and adherence to the protocol. Where potential issues are identified, they will be raised with the study sites to either amend the data or confirm it is correct.

The REDCap database service is managed by the University of Queensland. Original consent forms, paper copies of questionnaires and case report forms will be stored in a secure location accessible only to the local site investigator and the local research nurse at the site where the participant was recruited. These locally stored data will be in identifiable form as they will contain names, dates of birth and other identifiers.

After closure of the trial, investigators will retain all study documentation, including consent documents, ethics committee approvals, and correspondence for a minimum of 15 years or according to local policy before being securely destroyed.

### Confidentiality {27}

Participant records and the data generated by the study will be confidential in line with the recommendations of the NHMRC [60] and Australian privacy legislation [61]. Any information that may identify a participant will be excluded from data presented in the public arena. Data will be stored in a secure, lockable location, and access to electronic data will be protected through a password-protected web interface. The data extracted will be coded using a unique study number. Similarly, data collected on the electronic case report form will be coded using a unique subject number.

### Plans for collection, laboratory evaluation and storage of biological specimens for genetic or molecular analysis in this trial/future use {33}

No additional biological samples outside those collected as part of routine clinical care are being collected from participants.

## Statistical methods

### Statistical methods for primary and secondary outcomes {20a}

Data will be analysed at the individual patient level. The primary outcome, Goal Attainment Scaling (GAS) scores at three months, will be analysed using a linear regression model with the intervention group as a binary covariate and baseline GAS score as a continuous covariate. To allow for the clustering of data within study centres, inference will be based on robust standard errors. Multiple imputation will be used if there is more than 5% missing data on the three-month GAS scores. Subgroup analysis of GAS scores at three months will be undertaken based on baseline characteristics of patients (including age, CKD stage, and frailty status) and study site (including unit size). Subgroup effects will be assessed via treatment-by-subgroup interactions in linear regression models.

Repeatedly measured continuous secondary outcomes (GAS scores at 6 and 12 months, EQ-5D-5L scores, FI) will be analysed using mixed models for repeated measures (MMRM) with a random intercept for the study centres and an unstructured variance–covariance matrix to model the within-patient correlation structure due to the repeated measurements. The models will have fixed effects for the intervention group, categorical time, the intervention-by-time interaction, and baseline measurements of the outcome. The primary results will be the treatment effect estimates at 6 and 12 months and 95% confidence limits.

Other secondary outcomes will be analysed using regression models appropriate for the type of outcome. The effect of CGA on the rate of hospital admission will be tested using a Poisson regression model with a random intercept for study centres and the effect of CGA on time to all-cause mortality and time to hospital admission will be assessed using Cox regression with frailty (random intercepts) for study centres. A detailed statistical analysis plan will be made public before unblinding of the trial statistician and other study personnel at the coordinating centre.

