### Sample size {14}

Based on data from community-dwelling frail older adults, it is estimated that CGA will improve the GAS score by at least 10 points from an average score of 36 at baseline (which presents a change in one standard deviation, equivalent to a medium effect size) [25].

It is estimated that a cluster randomised trial with an average cluster size of 20 participants (coefficient of variation of sizes = 1) would require 16 hospital sites (clusters) with 8 sites in the intervention and control arm, respectively, to achieve 90% power to detect a mean difference in GAS score of 10 units at 3 months follow-up. This power calculation, giving a sample size of 320, assumes a common standard deviation of 10 units and an intra-cluster correlation coefficient of 0.3. To achieve sufficient power for the analysis of the secondary outcome of GAS at 12 months, an allowance for a 33% loss to follow-up over the 12 months was included, requiring baseline GAS observations from 478 participants. The 16 sites will be expected to each have a minimum of 55 patients who meet the eligibility criteria. Based on previous studies, it is estimated that approximately 10% of eligible patients will not consent to participate [26, 29] and a further 35% will not meet the frailty criteria [38] leaving a recruitment target of 500 (approximately 30 at each site). Assumptions in the sample size calculation will be re-estimated on trial data at the mid-point of the planned recruitment period.

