### Methods for additional analyses (e.g. subgroup analyses) {20b}

Subgroup analysis may be undertaken based on participant (age, CKD stage, frailty) and study site (region, size) characteristics where possible.

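### The primary model adjusts only for baseline GAS, which probably varies little, and omits age, CKD stage and baseline frailty, although these are already collected and could differ between arms

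*Protocol article*

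**What the plan says.** The section on statistical methods for primary and secondary outcomes {20a} specifies, for GAS at 3 months, a "linear regression model with the intervention group as a binary covariate and baseline GAS score as a continuous covariate". Clustering is handled by robust standard errors. No other covariate is named.

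The same section uses "baseline characteristics of patients (including age, CKD stage, and frailty status" for subgroup analyses, tested through treatment-by-subgroup interactions. Section {20b} returns to these variables only in that role: "Subgroup analysis may be undertaken based on participant (age, CKD stage, frailty) and study site (region, size) characteristics where possible". Section {20c} lists protocol deviations and imputation as the sensitivity analyses. No covariate-adjusted analysis appears anywhere.

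The Goal attainment scaling section describes "identifying goals; defining the current (baseline) status; identifying potentially better and worse attainment outcomes on a five-point scale" and gives the score formula, in which each goal has a "weight assigned to the goal area". It does not say at which level current status is placed, how many goals are set or what range the weights take. Sample size {14} assumes an improvement of 10 points "from an average score of 36 at baseline", an SD of 10 and an intra-cluster correlation (ICC) of 0.3.

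On allocation and recruitment, 16 hospitals are allocated 1:1 from a block schedule, with no stratification mentioned {16a}. The site principal investigator or a delegate identifies and approaches candidates {15}, and "clinicians and participants will not be blinded to the treatment allocation" {17a}.

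**The concern.** A single baseline covariate earns its place if it predicts the outcome or captures differences between the arms in who was recruited. Baseline GAS may do little of either. Its value depends on how many goals were set, how they were weighted and where the starting point was placed. If the starting point is usually the same, participants hardly differ on it, and it cannot stand in for age, kidney function or frailty.

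This matters more than usual in this design. With 8 hospitals per arm, chance imbalance in case mix is larger than in an individually randomised trial of the same size. Recruitment happens inside hospitals that are each wholly in one arm, so selection can also differ by arm. The variables that would describe such differences are to hand, but the primary estimate does not use them.

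**Working it through.** **1. What the assumed baseline mean implies.** Inputs: the GAS formula and the mean of 36. With n goals of equal weight, all starting at −1:

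baseline GAS = 50 − 10n / √(0.7n + 0.3n²)

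| Goals | Baseline GAS |
|---|---|
| 1 | 40.0 |
| 2 | 37.6 |
| 3 | 50 − 30/√4.8 = 36.3 |
| 4 | 35.5 |
| 5 | 34.9 |

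Three goals at −1 reproduce the plan's 36. All goals at −2 give 30.0 down to 19.8 for 1 to 5 goals, which does not fit.

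**2. How much baseline GAS would vary.** These are simulated values with assumed numbers of goals (3 only, 2 to 5, or 1 to 5) and weights (equal, or 1 to 3).

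| Goals starting at −2 | Mean | SD |
|---|---|---|
| None | about 36 to 37 | about 1.0 with 2 to 5 goals; 1.7 to 1.8 with 1 to 5 |
| 5% | 35.4 to 36.5 | 1.7 to 2.6 |
| 10% | about 35 to 36 | 2.4 to 3.2 |
| 25% | about 33 to 34 | 3.4 to 4.2 |

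An SD of about 1 to 3 is therefore compatible with a mean near 36. If each baseline point carried one point at 3 months (assumed slope 1), baseline would explain 1²/10² = 1% to 3²/10² = 9% of outcome variance.

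**3. Size of plausible chance imbalance.** For a covariate with ICC 0.05 to 0.10 (assumed), 8 hospitals per arm and 20 participants each, the SD of the arm difference in covariate SD units is √[(2/8)(ICC + (1 − ICC)/20)] = 0.16 to 0.19. With the plan's coefficient of variation of cluster size of 1 and equal weight per participant, it is √[(2/160)(1 + 39 × ICC)] = 0.19 to 0.25. A 0.2 SD imbalance is thus ordinary. One of 0.4 SD is 1.6 to 2.1 such SDs with unequal clusters, and one of 0.6 SD is 2.4 to 3.1. The last would more likely need selective recruitment as well.

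**4. Bias from an omitted factor.** Bias ≈ r × D × 10, where r is the factor's correlation with the outcome (assumed 0.1 to 0.3, with the factor unrelated to baseline GAS) and D is the imbalance in SDs (0.2 to 0.6):

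- low end: 0.1 × 0.2 × 10 = 0.2 points
- high end: 0.3 × 0.6 × 10 = 1.8 points

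**5. Precision.** The between-site part of the variance of the treatment effect is 2 × (0.3 × 100)/8 = 7.5. With a mixed model's weighting and a coefficient of variation of 1, the design effect is 6.7/0.906 = 7.39 and the total is 2 × 100 × 7.39/160 = 9.24. These inputs give 90.8% power (normal approximation, two-sided 5% assumed), close to the plan's 90%.

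- If the covariates explain 10% of within-site variance only, the reduction is 0.1 × (9.24 − 7.5)/9.24 = about 2%. The planned regression weights participants equally, so its total is 2 × 100 × 12.7/160 = 15.9, of which 2 × 70/160 = 0.875 is within-site, and the reduction is about 0.6%.
- If they explain 10% of between-site variance, the reduction is 0.75/9.24 = 8%, or 1.5/15.9 = 9% under the planned regression.

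**The case against.** The strongest case on the other side has five parts.

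- **Baseline GAS as a constant.** A reader might infer from the match with three goals at −1 that baseline GAS is effectively fixed. The documents do not support that. They state no starting level, and the 36 comes from a cited study of community-dwelling people. A baseline SD of about 3 still fits that mean, and some goals starting above −1 would widen it further. This stands.
- **Baseline adjustment as empty.** This would also go too far. Adjusting for baseline GAS is not an error, and the number of goals it reflects also sets the scale of the 3-month score. This stands.
- **Allocation known at recruitment.** The order of cluster randomisation and recruitment is not written, and the blinding statement concerns clinicians and participants. It also describes outcome assessors as blinded, so it cannot be asserted that unblinded staff set the goals. Knowledge of the arm is nonetheless probable. Every participant at a hospital receives the same arm, and the assessment is due within 14 days of baseline GAS, so the arm would show after the first few enrolments.
- **Prognostic value unknown.** Nothing in the article shows that age, CKD stage or FI predicts 3-month GAS. Goals are set with the patient's circumstances in mind, and eligibility narrows the range of all three variables. This stands and limits any claim about size.
- **A matter for the analysis plan.** A detailed statistical analysis plan is announced, and the article mentions no stratification without ruling it out. But the primary model is stated, not left open, so commenting on it is fair.

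**Conclusion.** The point holds as a recommendation to strengthen a stated choice. The primary model is not invalid, and the sample size does not depend on this point. The model relies on one covariate that probably has an SD of about 1 to 3 against 10, and it omits three recorded variables in a design where imbalance in them is plausible.

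The benefit cannot be fixed from the document. On the assumed correlations and imbalances, removable bias is about 0.2 to 1.8 points against the planned 10. The upper end needs both a fairly prognostic factor and an imbalance larger than chance alone would usually give. The reduction in variance is about 2% or less if only 10% of within-site variance is explained, and 8% to 9% if 10% of between-site variance is explained.

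A reader might turn the second case into a gain in power. That is not supported: the share explained is assumed, and the 9.24 belongs to a mixed model, whereas the plan uses linear regression with robust standard errors. No power figure should be quoted for this change. Nor would adjustment cure recruitment bias, because differences in motivation or choice of goals are not measured by these variables.

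**What to change.** Before unblinding, pre-specify in the protocol and the statistical analysis plan that the primary model includes age (continuous), CKD stage (3, 4, 5 without dialysis, dialysis) and baseline FI (continuous) as patient-level covariates beside baseline GAS. Keep the model with baseline GAS only as a named sensitivity analysis. State also at which level baseline goals are scored and how many goals are set, so that readers can judge what the baseline adjustment does.

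The cost is a few lines of text. Age and CKD stage are eligibility items and FI is measured before enrolment, so no new data are needed. The model gains five parameters (one for age, three for CKD stage, one for FI). With 16 clusters this is a small downside, because patient-level covariates use almost no between-cluster degrees of freedom. The covariates should be fixed now, since choosing them after unblinding would not be credible.

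### The primary test relies on robust standard errors with 16 unequal clusters and no named small-sample method; default versions would give about 10–16% type I error at the planned size variation

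*Protocol article*

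**What the plan says.** The section Statistical methods for primary and secondary outcomes {20a} of the protocol article analyses the three-month GAS score at patient level, by a "linear regression model with the intervention group as a binary covariate and baseline GAS score as a continuous covariate". Clustering enters in one sentence: "To allow for the clustering of data within study centres, inference will be based on robust standard errors". The section does not say which robust variance is meant, against which distribution the test statistic is referred, or how the small number of hospitals is handled. It promises a detailed statistical analysis plan, to be made public before unblinding, which is not at hand.

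The section Sample size {14} sets the conditions in which this method must work. The planned cluster sizes are given as "average cluster size of 20 participants (coefficient of variation of sizes = 1"). On that basis the section arrives at 16 hospitals, split evenly into 8 per arm. The calculation also "assumes a common standard deviation of 10 units and an intra-cluster correlation coefficient of 0.3".

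The same statistical section handles centres differently for the secondary outcomes. The repeated-measures models have a centre random intercept, the admission rate is "tested using a Poisson regression model with a random intercept for study centres", and the Cox models have a centre frailty term. The primary analysis is the exception.

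**The concern.** The treatment varies only between hospitals, so the evidence about its effect comes from 16 independent units. The cluster sandwich estimates the variance of the effect from the residual total of each hospital. It is justified when there are many clusters. With 8 per arm and very unequal sizes, two things go wrong:

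- The few large hospitals pull the fitted arm mean towards themselves. Their residuals shrink, and the variance is estimated too low.
- The variance estimate is itself unstable, so normal critical values, or t values on 14 or 15 degrees of freedom, are too small.

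Both errors act in the same direction. Confidence intervals would be too narrow and p-values too small for the trial's single primary comparison, and a positive result could not be read at the nominal 5% level.

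**Working it through.** **Inputs.** From Sample size {14}: 16 clusters (k = 8 per arm), mean size m = 20, CV = 1, SD = 10, ICC ρ = 0.3, difference 10. From Statistical methods {20a}: unweighted regression on arm and baseline GAS with robust standard errors. Assumed: two-sided α = 0.05, because the article states no α for the primary test.

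**Step 1: reproduce the plan's own figure.** The plan claims 16 sites suffice "to achieve 90% power to detect a mean difference in GAS score of 10 units at 3 months follow-up", with "This power calculation, giving a sample size of 320".

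- Design effect with equal clusters: 1 + (20 − 1) × 0.3 = 6.70.
- Allowing for unequal sizes in an efficiently weighted analysis: λ = mρ/(mρ + 1 − ρ) = 6/6.7 = 0.896, and the design effect is 6.70/(1 − CV²λ(1 − λ)) = 6.70/0.906 = 7.39.
- Effective n per arm: 160/7.39 = 21.6. Standard error: 10 × √(2/21.6) = 3.04. Power with normal quantiles: Φ(10/3.04 − 1.96) = 90.8%. This needs 7.8 clusters per arm, which rounds up to 8.
- Allowance for loss: 320/0.67 = 478, as stated.

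So the stated 90% is reproduced by an analysis that weights sites efficiently, as a mixed model does.

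**Step 2: the same inputs under unweighted regression.** The design effect is 1 + ((CV² + 1)m − 1)ρ = 1 + 39 × 0.3 = 12.7. Effective n per arm is 160/12.7 = 12.6, the true standard error is 10 × √(2/12.6) = 3.98, and power is 70.9% with normal quantiles (64.6% with t on 14 df).

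**Step 3: type I error by simulation under no effect.** Each simulated trial had 16 clusters split 8 v 8, normal site effects, an individual-level baseline covariate, and least squares on arm and baseline. There were 6,000 trials per scenario, with a Monte Carlo standard error of about 0.3–0.5 points. Rejection rates (%) at nominal 5%:

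| Sizes | Plain, normal | G/(G−1)-type factor, normal | Same, t15 | Same, t14 | Jackknife, t14 |
|---|---|---|---|---|---|
| CV 1, gamma, mean 20 | 16.2 | 14.9 | 12.0 | 11.8 | 6.3 |
| CV 1, lognormal, mean 20 | 14.4 | 13.2 | 10.4 | 10.1 | 5.5 |
| CV 1, gamma, mean 30 | 16.2 | 14.9 | 12.3 | 12.0 | 6.2 |
| CV 1, gamma, mean 20, ICC 0.05 | 14.8 | 13.8 | 11.2 | 11.0 | 6.1 |
| CV 0.7, gamma, mean 20 | 13.9 | 12.4 | 9.3 | 9.1 | 5.6 |
| CV 0.5, gamma, mean 20 | 10.3 | 9.4 | 7.4 | 7.2 | 5.1 |
| Equal, 20 each | 8.9 | 8.0 | 5.9 | 5.8 | 4.6 |

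ICC is 0.3 except where shown. The CV realised in 16 sampled sites averaged 0.94 (gamma, mean 20) and 0.87 (lognormal), slightly milder than the planned 1. A repeat with 4,000 trials per scenario gave 15.8% (plain, normal) and 11.9% (factor, t15) at CV 1, and 4.2–5.8% for the jackknife across all size patterns.

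**Step 4: size of the standard-error bias.** At CV 1 the mean estimated standard error was 2.9–3.1 against a true 3.7–4.0, which is 19–25% too small. In one run it was 2.89 against 3.74, a ratio of 0.773. That alone turns the 1.96 cut-off into 1.96 × 0.773 = 1.515, which a standard normal variable exceeds in absolute value about 13% of the time. The instability of the estimate accounts for the rest of the roughly 16%.

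**Step 5: the alternatives.** A random-intercept mixed model with 14 df rejected in 5.0–5.5% of null trials (2,500 per scenario). Least squares with the bias-reduced (CR2) sandwich and Satterthwaite df, which averaged 6–7, rejected in 6.8–7.6% (1,200 trials). With a true effect of one residual SD (10 points) at CV 1, the jackknife test with t14 had 67.3% power (4,000 trials).

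**The case against.** The strongest reply is that the article is silent rather than wrong. Bias-reduced and jackknife estimators are also robust standard errors, so a sound analysis would comply with the sentence as written. The choice of variance variant and degrees of freedom is commonly left to the analysis plan. This stands as a limit on wording. A reader might infer that the plan prescribes an uncorrected sandwich with normal critical values, but nothing in the text says so. It does not remove the point. The article fixes the class of method for the primary test, and at the planned CV the usual software versions of that method fail, including the one with a finite-cluster factor and t15. An analysis plan that only carries the sentence forward would inherit the problem.

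Second, 10–16% might be taken as the trial's actual error rate. The documents do not support that. CV 1 is a planning input, and the same section aims for about 30 participants per site. With equal sites the error is about 6–9%. On the other side, the sponsor chose CV 1, the setting mixes tertiary and peripheral hospitals, and every uncorrected version simulated exceeded 5%.

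Third, it is tempting to extend the criticism to the secondary mixed, Poisson and Cox models. That is not supported. Their degrees of freedom are ordinary analysis-plan detail, and there is no adequate calculation for them here. The point is confined to the primary analysis.

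**Conclusion.** The concern holds for the primary analysis, conditionally. With 16 clusters, 8 per arm, and a two-sided 5% test (assumed), the plain or G/(G−1)-corrected cluster sandwich has a type I error of about 10–16% at the planned CV of 1, and about 6–9% if sites are nearly equal. At CV 1 the result changes little between mean sizes of 20 and 30 or between ICCs of 0.05 and 0.3, so size imbalance and the small number of clusters drive it. The conclusion concerns the usual versions of the named method under the plan's own inputs. It does not say that the sponsor has ruled out a correction.

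There is a linked inconsistency: the stated 90% power matches an efficiently weighted analysis, not the unweighted regression that the article names.

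**What to change.** State in the protocol and analysis plan, before unblinding, that primary inference comes from a linear mixed model with a random intercept for hospital, arm and baseline GAS as fixed effects, REML estimation, and Kenward-Roger or 14 between-cluster degrees of freedom. This agrees with the centre effects already planned for the secondary outcomes and with the weighting behind the 90% power.

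If ordinary regression is kept, name the variance and its reference distribution: CR2 with Satterthwaite degrees of freedom, or a CR3/jackknife cluster variance with t on 14 df. These bring the error to about 4–8%; CR2 (6.8–7.6%) is improved but not fully nominal. State the α level and sidedness as well.

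The change needs only wording and standard software options, but it has statistical costs:

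- Intervals become wider.
- A mixed model weights hospitals differently from patient-level regression, and the plan should say so.
- By the formula in step 1, mixed-model power with t on 14 df is 86.4% rather than 90.8%.
- Under ordinary regression at CV 1, power is about 67% in simulation with corrected inference, and 71% by formula with normal quantiles. The 90% claim would have to be restated.

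The power figures take 10 as the residual SD after baseline adjustment. If baseline GAS explains outcome variation, they would be higher. The sample-size re-estimation planned at mid-recruitment is a natural place to use the observed CV and the chosen method together.
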